### Scientific Objectives

The overall aims of this project are to determine whether scarcity and future discounting are associated with medication adherence in children with asthma and to explore their role in the relationship between unmet social needs and adherence. Using a prospective observational study, we will investigate three primary relationships:

The relationship between scarcity, future discounting, and adherence to asthma controller medication;The association between unmet social needs, scarcity, and future discounting; andThe potentially mediating role of scarcity and future discounting on the relationship between unmet social needs and adherence to medication in children with asthma.

Our hypotheses related to each of these three primary relationships are the following:

We hypothesize that individuals experiencing scarcity and those with higher rates of future discounting will have lower adherence to asthma controller medication.We hypothesize that unmet social needs will be related to scarcity and future discounting in the following ways:Parents reporting unmet social needs will be more likely to experience scarcity and have greater levels of future discounting;The number of unmet social needs will correlate with level of scarcity and future discounting; andImprovements in a family’s unmet social needs during the study period will be associated with decreased scarcity and future discounting rates.We expect that scarcity and future discounting will play a mediating role in the relationship between unmet social needs and adherence to medication, with higher levels of both scarcity and future discounting specifically amplifying the impact of unmet social needs on medication adherence.

We will also examine two exploratory aims:

Examine whether adherence to medication mediates the association between unmet social needs and asthma outcomes: asthma control, ED visits, and hospitalizations.Document the progression of unmet social needs as the world moves to the next phase of the COVID-19 pandemic.

This project will help understand the relationship between cognitive factors, medication adherence, and unmet social needs, opening the door to developing targeted interventions to improve adherence to medication and, ultimately, children’s health outcomes.

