### Follow-up Measures

At 6 and 12 months, we will assess health service use, specifically asthma-related ED visits and hospitalizations, via parental reports as well as the patient’s hospital file and provincial health insurance data. We will also measure access to resources to address unmet social needs for participants who agreed to be referred to a social worker at their local community services center using a single-item question for each identified unmet social need (eg, “Since you entered this study, have you been in contact with a social worker or someone from the local community services centre to help you access resources for [identified unmet social needs]?”)

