### Statistical Analysis

Results will be reported following the recommendations of the Strengthening the Reporting of Observational Studies in Epidemiology Statement for cohort studies [100]. For *aim 1*, we will first perform descriptive statistics for our measures of executive function (accuracy and time to complete the Eriksen flanker task between easy and hard scenarios) at baseline, 6 months, and 12 months and model trajectories using mixed effects regression models. We will then quantify the relationship between both level of scarcity at baseline and trajectories with PPDC in the 12 months following the index visit. We will use unadjusted linear regression models, before adjusting for potential confounders, including sociodemographic factors (eg, child age and sex) and disease characteristics (eg, PPACI at baseline and class and dosing frequency of controller medication). We will perform collinearity diagnostics on potential confounders, and if significant correlation is identified, we will adjust our model accordingly. Exploratory analyses will use logistic and ordinal regression models and the same set of variables to examine any effect of scarcity on health service use (ED visit or hospitalization). We will use the same analysis plan to examine the relationship between future discounting (using Kirby’s discount parameter) and PPDC.

For *aim 2*, we will first assess whether scarcity and future discounting scores at baseline differ between families with versus those without unmet social needs. In the subgroup with identified unmet social needs at any time during the study, we will use regression models with time-varying exposure to estimate the effect of referral to social services and access to services on the presence of unmet social needs (ie, determine if referral to social services led to improvement in unmet social needs). We will then use generalized estimating equations to estimate the effect of unmet social needs on cognitive capacity, executive control, and future discounting.

For *aim 3*, we will evaluate whether scarcity is a mediator of the relationship between unmet social needs and adherence with multiple regression models using a recognized approach [101]. We will use a similar analysis for future discounting.

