For *aim 4*, we will use multivariable logistic regression models to examine the effect of unmet social needs on ED visits (any vs none) and hospitalizations (any vs none), testing whether there is an interaction between medication adherence and unmet social needs in this relationship (whether better adherence is protective in children with unmet social needs). A similar approach will be used for asthma control using an ordinal regression model for the 4-point PPACI.

For *aim 5*, we will use descriptive statistics to document the prevalence of unmet social needs in our sample as well as within families and use logistic regression models to test whether referrals to social services modulate those trajectories.

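### Aim 2 judges improvement after referral by the presence of unmet social needs, an outcome that at family level cannot register a partial reduction

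*Protocol article*

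**What the plan says.** The aim 2 paragraph of Statistical Analysis has three steps.

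- It first asks whether "scarcity and future discounting scores at baseline differ between families with versus those without unmet social needs".
- Then, "In the subgroup with identified unmet social needs at any time during the study", it says "we will use regression models with time-varying exposure to estimate the effect of referral to social services and access to services". The outcome of that step is the "presence of unmet social needs (ie, determine if referral to social services led to improvement in unmet social needs".
- Last, generalized estimating equations relate unmet needs to cognitive capacity, executive control and discounting.

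For aim 5 the plan will "use logistic regression models to test whether referrals to social services modulate those trajectories".

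The data are finer than presence or absence. Table 1 and Main Predictors list about eight domains of need (employment, housing, utilities, financial strain, food, transportation, childcare, education and health literacy), measured at recruitment, 6 and 12 months. Follow-up Measures asks about access to help "using a single-item question for each identified unmet social need".

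Hypothesis 2 in Scientific Objectives has three parts. The first compares parents who report needs with those who do not. The second is "The number of unmet social needs will correlate with level of scarcity and future discounting". The third concerns improvement: better "unmet social needs during the study period will be associated with decreased scarcity and future discounting rates". No analysis for aims 1 to 5 names the number of needs in a model or defines improvement.

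**The concern.** The stated outcome and the stated question differ for any family with more than one need. If presence means at least one need in the family, improvement is recorded only when every need has gone. The outcome is then least responsive in families with the most needs, where a partial gain is most likely to be the result of referral.

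The group is small: about 50 families on the plan's own assumption in Power Calculation and Feasibility, before missing data and loss. Discarding information already collected could leave a real reduction in needs undetected.

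**Working it through.** **1. The plan's own figure.** No power is stated for the referral analysis. The nearest figure is 85% power for a 16-point difference in adherence between families with and without needs. With SD 33 and groups of 50 and 150, the standard error is 33 × √(1/50 + 1/150) = 5.39. Then 16/5.39 = 2.97, and Φ(2.97 − 1.96) = 0.84. The figure reproduces. It supplies the 50 families used below but says nothing about the effect of referral on needs.

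**2. Scoring.** Under a family-level presence outcome, four needs at baseline and one at follow-up gives present, then present: no change. With one need per family, presence and count are the same variable and nothing is lost.

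**3. Dependence on the number of needs.** Assume 25 families referred and 25 not, each starting with k needs that resolve independently with probability 0.5 if referred and 0.2 if not. The chance that no need is left is 0.5^k against 0.2^k. Power is from a two-sided 5% two-proportion test.

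| k | Cleared, referred | Cleared, not referred | Power |
|---|---|---|---|
| 1 | 0.50 | 0.20 | 0.61 |
| 2 | 0.25 | 0.04 | 0.56 |
| 3 | 0.125 | 0.008 | 0.38 |
| 4 | 0.0625 | 0.0016 | 0.23 |

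**4. Presence against count.** Simulation of 50 families, half referred, with the same resolution probabilities, one follow-up visit and no confounding (4,000 replicates). The count is analysed by ANCOVA on the baseline number. Relative loss is 1 − (any-need power ÷ count power), using the unadjusted any-need test.

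| Mean needs | Within-family correlation of resolution | Any need | Any need, adjusted for baseline number | Count, adjusted | Relative loss |
|---|---|---|---|---|---|
| 1.5 | 0.05 | 0.565 | 0.580 | 0.752 | 25% |
| 1.5 | 0.3 | 0.573 | 0.575 | 0.671 | 15% |
| 1.5 | 0.6 | 0.607 | 0.589 | 0.599 | none |
| 2.2 | 0.05 | 0.485 | 0.495 | 0.868 | 44% |
| 2.2 | 0.3 | 0.551 | 0.546 | 0.755 | 27% |
| 2.2 | 0.6 | 0.587 | 0.573 | 0.614 | 4% |
| 3.2 | 0.05 | 0.386 | 0.377 | 0.960 | 60% |
| 3.2 | 0.3 | 0.484 | 0.473 | 0.836 | 42% |
| 3.2 | 0.6 | 0.561 | 0.541 | 0.701 | 20% |

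The loss exceeds half in 1 of 9 settings. Applying the plan's 30.4% allowance, 50 × 0.696 ≈ 35 families remain. With 35 families, with and without new needs arising (1,500 replicates), the loss exceeds half in 6 of 18 settings (worst 0.14 against 0.81) and is nil in the mildest.

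**5. Where the gain comes from.** A second simulation (2,000 replicates, 50 families, half referred, between-family variation in resolution) separates the count from the baseline adjustment.

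| Mean needs; resolution, referred vs not | Any need | Any need, adjusted | Count | Count, adjusted |
|---|---|---|---|---|
| 2; 50% vs 25% | 0.42 | 0.40 | 0.45 | 0.61 |
| 2; 40% vs 20% | 0.26 | 0.26 | 0.30 | 0.47 |
| 1.2; 50% vs 25% | 0.44 | 0.42 | 0.41 | 0.49 |

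In the first row the total gain is 0.61 − 0.42 = 0.19. The count alone gives 0.45 − 0.42 = 0.03, and baseline adjustment of the count adds 0.61 − 0.45 = 0.16. Adjusting the any-need outcome gains nothing, so the benefit needs the count and the baseline number together.

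**The case against.** **The aim 2 sentence does not say that presence means at least one need.** It names neither a link function nor a unit of analysis. For emergency visits and hospitalizations the authors do spell out the dichotomy. Presence of each separate need, clustered by family, would fit the wording, the domain-level measurement and the per-need access question. This stands: a need-by-need reading is not excluded. The family-level reading remains the more natural one. The same paragraph contrasts families with and without needs, the power section counts families with at least one need, and aim 5 uses logistic models.

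**Coding of variables is commonly left to the analysis plan.** True in general, but here the article fixes an outcome and equates it with a different construct.

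**The simulations are not the planned analysis.** They use one follow-up visit and a fixed exposure, whereas the plan has time-varying exposure, two follow-ups and families whose needs may first appear later. Needs per family, resolution rates and the share referred are all assumed. This stands, and the power figures are illustrations only.

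**The baseline comparison is not at fault.** A reader might infer that comparing families with and without needs contradicts hypothesis 2. It does not: that comparison tests the hypothesis's first part. Only the second part, on the number of needs, has no named analysis.

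**Conclusion.** The mismatch is real: presence is not improvement, and at family level it cannot record a partial reduction. With about 50 families, the cost in power runs from about nil to 60%, depending on how many needs families hold and how far they resolve together. All of these figures rest on assumptions that the documents do not supply.

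A reader might infer that most of the power is lost. The documents do not support that: a loss above half appears only with several needs per family and low to moderate correlation, and much of the gain at 50 families comes from baseline adjustment. Nor do they support a prediction that a null result would be read as showing that referral does not help.

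The analysis is an intermediate step in aim 2 and a test within exploratory aim 5. The primary outcome is untouched. Referral goes only to families who want it, and neither outcome removes that confounding. The point is a cheap, worthwhile improvement to a non-primary analysis.

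**What to change.** In the aim 2 paragraph of Statistical Analysis:

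- Make the outcome of the referral and access analysis the number of unmet needs at 6 and 12 months, adjusted for the number at baseline, in a count or ordinal model that allows for within-family correlation. Alternatively, take each identified need as resolved yes or no, clustered by family. The count also captures new needs; the need-by-need version captures only those already identified.
- Use the same outcome for the aim 5 referral test.
- Keep any need versus none as a descriptive summary.
- Keep the with/without comparison at baseline, and add the number of needs as a trend term to test the second part of hypothesis 2.

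If a need-by-need outcome was always meant, one sentence stating the unit of analysis and the clustering settles the aim 2 outcome.

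The cost is analysis wording only, because every item is already collected. The downsides are that a count weights all domains equally and is slightly less simple to report.

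### The exploratory aim asks whether adherence mediates the effect of unmet social needs on asthma outcomes, but the stated analysis tests only an interaction

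*Protocol article*

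**What the plan says.** Scientific Objectives lists three primary relationships and then two exploratory aims. Statistical Analysis numbers its aims 1 to 5, so the first exploratory aim is aim 4, and the matching outcomes confirm this.

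- **Aim as stated (Scientific Objectives):** "Examine whether adherence to medication mediates the association between unmet social needs and asthma outcomes", the outcomes being asthma control, ED visits and hospitalizations.
- **Analysis as stated (Statistical Analysis, aim 4):** "we will use multivariable logistic regression models to examine the effect of unmet social needs on ED visits (any vs none) and hospitalizations", followed by "testing whether there is an interaction between medication adherence and unmet social needs in this relationship". The article explains the test as "whether better adherence is protective in children with unmet social needs".
- **Asthma control:** "A similar approach will be used for asthma control using an ordinal regression model for the 4-point PPACI".

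Two sentences bear on the secondary point. Hypothesis 3 says that "scarcity and future discounting will play a mediating role in the relationship between unmet social needs and adherence to medication", and adds "with higher levels of both scarcity and future discounting specifically amplifying the impact of unmet social needs on medication adherence". For aim 3, Statistical Analysis says "we will evaluate whether scarcity is a mediator of the relationship between unmet social needs and adherence with multiple regression models", following a cited approach, with a similar analysis for future discounting.

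**The concern.** Mediation and effect modification are different questions. Mediation asks whether families with unmet needs have worse outcomes because their children's adherence is lower. Effect modification asks whether adherence matters more, or less, in families with needs than in families without. The aim poses the first and the analysis tests the second. The article's own explanation of the test describes protection within the group with needs, so the word interaction is not just being used loosely.

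This is not a detail left to an analysis plan. The article names a specific test for a specific aim. An analysis plan that followed it would leave the aim unanswered, and one that estimated mediation would depart from the published text. The practical risk is in interpretation: a null interaction could be read as evidence against a pathway through adherence, and a non-null one as evidence for it. Neither inference would be valid.

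**Working it through.** The plan gives no figure on this point, so there is none to reproduce. The check has two parts: algebra, and a simulation with assumed coefficients.

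**Algebra (linear case).** Let X be unmet needs, M adherence and Y the outcome.

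- Mediator model: E[M | X] = a0 + a·X
- Outcome model: E[Y | X, M] = b0 + c·X + b·M + d·X·M

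The aim 4 test is a test of d = 0. The pure natural indirect effect is a·b and the total natural indirect effect is a·(b + d).

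1. If d = 0, both equal a·b, the total effect is c + a·b, and the proportion mediated is a·b / (c + a·b). With a = 0 this is 0%. With c = 0 and a·b not zero it is 100%. With c and a·b of the same sign it can lie anywhere between. A zero interaction therefore leaves the degree of mediation open.
2. If a = 0, the indirect effect is 0 whatever d is. A clear interaction therefore does not establish mediation.
3. If a and d are both non-zero, d does enter the total indirect effect. The product term is relevant to the indirect effect, but testing it is not a test of mediation.

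**Simulation.** All of these inputs are assumptions except the 25% prevalence of unmet needs and the sample of 200, which are in Power Calculation and Feasibility. Adherence is standardized (residual SD 1), the outcome is binary with intercept -1 on the log-odds scale, and the direct effect of needs is 0.2. In a logistic model a·b is only an approximate indirect effect on the log-odds scale, which is enough for this purpose.

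| Scenario | n | Set values | Estimated a | Estimated b | Interaction | a·b |
|---|---|---|---|---|---|---|
| Mediation only | 200,000 | a = -0.5, b = -0.6, d = 0 | -0.503 | -0.601 | 0.012 (p = 0.34) | (-0.503)(-0.601) = 0.302 |
| Interaction only | 200,000 | a = 0, b = -0.3, d = -0.5 | -0.004 | -0.303 | -0.495 (p < 0.001) | (-0.004)(-0.303) = 0.001 |

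In the first scenario there is a clear pathway through adherence and the planned test finds nothing. In the second there is no pathway and the planned test is strongly positive.

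Repeating the mediation-only scenario at the planned n = 200, the interaction test rejected in 4.2% of 1,000 runs at the 5% level. That is close to its nominal error rate: in this scenario the test has no power for the question the aim asks.

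**Hypothesis 3 beside the aim 3 analysis.** Objective 3, the main clause of hypothesis 3 and the aim 3 analysis all concern mediation and agree. The clause on amplification predicts a needs-by-scarcity and a needs-by-discounting interaction, and the analysis text names no test of either.

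**The case against.** Four points can be made on the plan's side.

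- **The components are mostly planned.** The abstract's primary analysis regresses adherence on unmet needs, and the aim 4 model relates the outcomes to needs with an adherence interaction. Regression-based mediation uses these two kinds of model. This stands, and it makes the repair cheap. But no step that combines them into an indirect effect is stated.
- **The aim is exploratory.** This stands. It does not bear on the primary outcome, the primary comparison or the sample size.
- **Aim 3 may be sound.** A reader might infer that the same mismatch runs through aim 3, and that its mediation model is misspecified because it lacks a product term. The documents do not support this. Objective, main clause and analysis agree there, and the cited approach is not shown and may or may not include such a term. What remains is that the amplification clause has no named test. It could also be a loose description of how the mediators worsen adherence.
- **Nothing says that a null interaction would be misreported.** A reader might infer that the authors would present it as adherence playing no role. The article does not say so, and its explanation confines the test to protection in children with needs. The risk of misreading comes from pairing this test with that aim, not from a stated intention.

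One further overreading should be avoided: that the interaction carries no information on the indirect effect. With a product term, the total indirect effect is a·(b + d).

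**Conclusion.** The point holds for aim 4: the stated test addresses effect modification and cannot by itself answer the stated mediation aim. This follows from the text and the algebra. The simulation only illustrates it, and its size depends on the assumed coefficients.

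Severity is moderate, because the aim is exploratory and the main comparison of adherence is untouched.

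Even a correct mediation analysis would have a limit. Under Primary Outcome, PPDC covers the 12 months of follow-up, and under Follow-up Measures, ED visits and hospitalizations are collected at 6 and 12 months. Mediator and outcome therefore overlap in time, and an event could change later adherence.

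For hypothesis 3 the conclusion is narrower: one clause lacks a named test.

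**What to change.** 1. **Aim 4.** Add an estimate of the indirect effect of baseline unmet needs on each outcome (ED visits, hospitalizations, asthma control) through PPDC. Combine a needs-to-PPDC model with the outcome model, allow the product term, and give a bootstrap interval. Keep the interaction as a separate exploratory question. Alternatively, restate the aim as effect modification and leave the analysis as it is.
2. **Timing.** State as a limitation that 12-month PPDC and the follow-up outcomes overlap, or use PPDC from months 0-6 with outcomes from months 6-12. Table 1 assesses the asthma control index over the preceding 6 months, so its 12-month value fits the second window. The split uses a shorter period for both adherence and events, which costs precision.
3. **Hypothesis 3.** Report the needs-by-scarcity and needs-by-discounting product terms as the test of amplification, at a small loss of precision, or delete the amplification clause.

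The cost is wording and a modest amount of extra analysis. The planned data collection already covers unmet needs, PPDC, health service use and asthma control, so no additional participants or measurements are needed. Under Results, analysis starts only once recruitment is complete, so the wording can be settled beforehand.

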**Primary outcome**						
	*Adherence*^a^*:* Proportion of prescribed days covered	Number of days for which the drug was dispensed by a pharmacy divided by the number of days for which it was prescribed [63,70]	Pharmacy claims data (*Registre de données sur les Médicaments*)	—^b^	—	X^c^

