**Exploratory measures**						
	*Capability*	Perceived Competence Scale [85,86]	Questionnaire	X	—	—
	*Motivation*	Treatment Self-Regulation Scale (adapted for adherence) [87]	Questionnaire	X	—	—
	*Perceived stress:* perceived stress scale	4-item measure used to understand how respondents perceive stress and how their feelings are impacted by certain situations [88]	Questionnaire	X	X	X
	*Asthma severity*: PPACI^d^	4-level PPACI assessed in the preceding 6-month period. On the basis of the number of doses per week of short-acting beta-agonists, use of oral corticosteroids within 14 days of a medical claim or hospitalization for asthma, any ED visit for asthma, and any hospitalization for asthma [89]	Medical chart	X	X	X
	*Access to resources*	Whether families accessed resources to which they were referred (social worker at local community health center)	Questionnaire	—	X	X
	*Asthma treatment satisfaction*	Single item inquiring who is primarily responsible for the child’s asthma management and 1 question drawn from the Asthma Medication questionnaire [90] adapted to inquire specifically about management of one’s child’s asthma	Questionnaire	X	X	X
	*Asthma responsibility questionnaire*	10-item measure examining the division of asthma management responsibilities between child and parent [91]	Questionnaire	X	—	X

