**Covariates**						
	Child’s *age* and *sex*	N/A^e^	Medical chart	X	—	—
	Child’s *gender*	N/A	Questionnaire	X		
	*Caregiver’s relationship with child*	Two items interrogating relationship to the child and whether respondent is the child’s legal guardian	Questionnaire	X	—	—
	*Caregiver’s gender*	N/A	Questionnaire	X	—	—
	*Caregiver’s marital status* and *living situation*	Single items assessing marital status and living situation as it relates to the child	Questionnaire	X	—	—
	*Postal code of the child’s residence*	N/A	Questionnaire	X	—	—
	*Caregiver’s level of education*	Elementary school or less, some high school, high school graduate, some college or technical school, college graduate, or completed a graduate degree	Questionnaire	X	—	—
	*Household income*	One item question based on the Canadian income survey [92]	Questionnaire	X	—	—
	*Presence of a smoker or e-cigarette user in the house*	2 question items investigating use of tobacco products or e-cigarettes in the last month [93]	Questionnaire	X	X	X
	*Responsibility for asthma management*	“Who is responsible for asthma management?”	Questionnaire	X	—	—
	*Child’s ethnicity, immigration status*, and *language spoken at home*	Questions using categories from Canadian census [94]	Questionnaire	X	—	—
	*Class of controller medication received during study period*	Inhaled corticosteroids and long-acting beta-agonists of leukotriene receptor antagonists	Medical chart	X	X	X

^a^The name of the variable in question has been italicized.

^b^Em dashes in the timeline signify that data for the associated variable will not be collected at the time point in question.

^c^X in the timeline indicate data collection for the associated variable at the time point (recruitment, 6-month follow-up, or 12-month follow-up) in question.

^d^PPACI: Pediatric Pharmacoepidemiology Asthma Control Index.

^e^N/A: not applicable.

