### Primary Outcome

*Adherence to controller medication* will be measured for the 12 months of follow-up on a scale of 0%-100% by the *proportion of prescribed days covered (PPDC)*, a validated index calculated as the number of days for which the drug was dispensed by a pharmacy divided by the number of days for which it was prescribed [63]. The PPDC accounts for varying durations of physician prescriptions [70] and leads to conservative estimates of adherence, as possession of medication is a prerequisite for adherence but does not confirm its use. The PPDC will be calculated using medical records (prescriptions made by the clinician) and the reMed database [24,63]. reMed collects drug claims for both privately and publicly insured children.

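### Exploratory aim 4 reads adherence as protective, but the only adherence measure defined is a 12-month PPDC that partly follows the events it is meant to explain

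*Protocol article*

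**What the plan says.** Protocol article, Statistical Analysis, aim 4: logistic models relate unmet social needs to ED visits and to hospitalizations, each coded any versus none, and test an interaction between adherence and needs. The plan glosses this as "whether better adherence is protective in children with unmet social needs". An ordinal model of the four-level PPACI follows the same approach. Scientific Objectives describes adherence in this exploratory aim as a mediator between needs and asthma outcomes.

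Primary Outcome: adherence "will be measured for the 12 months of follow-up on a scale of 0%-100" percent, as the PPDC. Table 1 defines it as "Number of days for which the drug was dispensed by a pharmacy divided by the number of days for which it was prescribed" and marks it at 12 months only. Aim 1 uses the same window: "PPDC in the 12 months following the index visit".

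Follow-up Measures: "At 6 and 12 months, we will assess health service use, specifically asthma-related ED visits and hospitalizations". Table 1 describes asthma control as "4-level PPACI assessed in the preceding 6-month period", at recruitment, 6 and 12 months.

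Nowhere is PPDC lagged, ended at an event or updated over time. Time-varying exposure is named only for referral and access to services, under aim 2.

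**The concern.** In aims 1 and 3 adherence is the outcome, and a 12-month PPDC is a reasonable choice. In aim 4 it becomes an explanatory variable. To be protective, or to mediate, adherence has to come before the event. For a child with an ED visit at the end of month 3, nine of the twelve months of PPDC (75%) lie after the visit.

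If families collect more controller medication after a visit, the visit raises the variable meant to explain it. Children with events then look more adherent, and a protective association is weakened or reversed. If the response to a visit differs between families with and without unmet needs, a false interaction can also appear. The baseline PPACI adjustment listed for aim 1 would not remove a response to an event during follow-up.

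**Working it through.** **Plan's own figures.** None is given for aim 4. The PPDC inputs come from Power Calculation and Feasibility: mean 68, SD 33. With these, a 16-point difference at two-sided 0.05 and 80% power needs 134 to 136 participants (stated 135). Power for 50 against 150 is 84% (stated 85%). Neither figure is in dispute.

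**Step 1: windows side by side.**

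| Quantity | Months | Relation to PPDC (months 0-12) |
|---|---|---|
| ED visit, hospitalization (any versus none) | 0-12 | same window |
| 6-month PPACI | 0-6 | second half of PPDC is later than the outcome |
| 12-month PPACI | 7-12 | first half of PPDC precedes, second half is concurrent |

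Aim 4 does not say which PPACI reading is used.

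**Step 2: bias in the adherence-event association, no true effect.** Assumptions: 30% of children have a visit at a uniform time t in the year; underlying PPDC is normal (68, 33) with values outside 0-100 set to the limit; after the visit it rises by b points, capped at 100. Observed PPDC = [t × before + (12 − t) × after] / 12. On average half the year follows the visit, so b = 10 moves a child's PPDC by at most about 5 points on average. Results from 400,000 simulated children per row:

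| b | OR per 20 points, whole-year PPDC | OR, PPDC months 0-6 against first visits in months 7-12 |
|---|---|---|
| 0 | 1.00 | 1.00 |
| 10 | 1.11 | 1.00 |
| 15 | 1.17 | 1.00 |
| 20 | 1.23 | 1.00 |

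The last column excludes children with an earlier visit; adjusting for earlier visits instead also gives about 1.00.

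**Step 3: a different model, with and without a true effect.** Adherence is beta-distributed with mean 0.68 and SD 0.33. Annual event risk is 20% or 35%. After an event, 50% or 100% of uncovered days become covered for 3 or 6 months.
- No true effect: whole-year OR 1.09 to 1.47 per 25 points; lagged OR about 1.00.
- True protective effect (OR 0.76 to 0.78 without any refill response): whole-year OR 0.84 to 1.14; lagged OR 0.78 to 0.79.

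**Step 4: the interaction, which is what aim 4 tests.** The Step 2 model with 25% of families having needs (the plan's own assumption) and no effect of adherence in anyone:

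| Rise without needs | Rise with needs | Interaction OR per 20 points |
|---|---|---|
| 10, 15 or 20 | the same | 0.99 to 1.01 |
| 10 | 0 | 0.90 |
| 20 | 0 | 0.81 |
| 5 | 20 | about 1.17 |

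An equal response leaves the interaction essentially unbiased. The OR within the needs group is still biased whenever that group itself responds: with a 10-point rise in both groups it is about 1.12. With 0 points in the needs group, that group's OR is 1.00 and the false interaction comes from the families without needs.

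**Step 5: events left after lagging.** At 30% annual risk, 25% of 200 with needs and uniform timing: 50 × 0.30 × 0.5 = 7.5, about 8 children with needs and a first visit in months 7-12. With 135 analysed: 135 × 0.25 × 0.15 ≈ 5.

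**The case against.** **The refill response is not in the documents.** This stands. No section says that a visit raises dispensing. PPDC divides by days prescribed, so a new or extended prescription after a visit enlarges the denominator and could lower PPDC. The overlap of windows is a fact; the size and direction of the bias are assumptions.

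**The interaction need not be biased.** This also stands. A reader might infer that the interaction is distorted whenever visits prompt refills; Step 4 shows that it is not if the response is equal. The standard error of the log interaction OR at n = 200 is roughly 0.27 to 0.29, so a shift to 0.90 (0.11 on the log scale) is about 0.4 standard errors. What is exposed regardless of any difference between groups is the gloss about protection in children with needs.

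**Aim 4 does not restate its windows, and an SAP could lag them.** This stands in part. The aim says only medication adherence, and events are collected separately at 6 and 12 months, so a lagged analysis is possible. But the article does define adherence, once, over 12 months, and offers no other version. The time-order problem follows from what is stated, not from omitted detail.

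**It is exploratory.** Agreed. A reader might infer that the primary result is compromised. It is not: where adherence is the outcome, the 12-month PPDC is not touched by this point.

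**Conclusion.** The point holds for exploratory aim 4. As written, adherence is measured over the same 12 months as the ED visits and hospitalizations it is said to protect against, and over a partly overlapping period for the 12-month PPACI. The association cannot then be read as protection.

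Under assumed rises of 10 to 20 PPDC points after a visit, a null effect appears as an OR of 1.11 to 1.23 per 20 points, and under the second model a true OR near 0.77 per 25 points can appear as 0.84 to 1.14. The interaction moves to about 0.81 to 0.90 only if families without needs respond by 20 or 10 points and those with needs do not respond. That artefact would look like adherence being more protective in children with needs. These figures rest on the assumed event risk, timing and refill response, and an effect on the PPDC denominator could change the direction. The documents do not support reading this as a demonstrated bias of known sign, or as a defect in the primary analysis. It is an inexpensive improvement worth making.

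**What to change.** For aim 4 only, compute PPDC for months 0-6 from reMed and the prescription records. Relate it to ED visits and hospitalizations in months 7-12 and to the 12-month PPACI, which already looks back over that period.

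Show the results with and without adjustment for ED visits and hospitalizations in months 0-6. Those early events may lie on the pathway from unmet needs, so adjustment can remove part of the effect of interest. Without adjustment, an early visit that both changed dispensing and marks a child prone to later visits is left uncontrolled.

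Report the concurrent 12-month version as an association, not as a test of protection. Keep the 12-month PPDC as the primary outcome elsewhere.

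Cost: no new collection, provided that dispensing and event dates are available within the records already used. The price is clearly fewer events: about 8 of 50 children with needs under the assumptions in Step 5, or about 5 if 135 families are analysed. The interaction will be imprecise and should be presented as an estimate with its interval.
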